## Abstract

**Background:**

Twenty-to-forty percent of women experience postpartum depressive symptoms, which can affect both the mother and infant. In preterm infants, daily skin-to-skin contact (SSC) between the mother and her infant has been shown to decrease maternal postpartum depressive symptoms. In full-term infants, only two studies investigated SSC effects on maternal depressive symptoms and found similar results. Research in preterm infants also showed that SSC improves other mental and physical health outcomes of the mother and the infant, and improves the quality of mother-infant relationship. This randomized controlled trial will investigate the effects of a SSC intervention on maternal postpartum depressive symptoms and additional outcomes in mothers and their full-term infants. Moreover, two potential underlying mechanisms for the relation between SSC and the maternal and infant outcomes will be examined, namely maternal oxytocin concentrations and infant intestinal microbiota.

**Methods/design:**

*Design:* A parallel-group randomized controlled trial. *Participants*: 116 mothers and their full-term infants. *Intervention:* Mothers in the SSC condition will be requested to provide daily at least one continuous hour of SSC to their infant. The intervention starts immediately after birth and lasts for 5 weeks. Mothers in the control condition will not be requested to provide SSC. Maternal and infant outcomes will be measured at 2 weeks, 5 weeks, 12 weeks and 1 year after birth. *Primary outcome:* maternal postpartum depressive symptoms. *Secondary maternal outcomes:* mental health (anxiety, stress, traumatic stress following child birth, sleep quality), physical health (physical recovery from the delivery, health, breastfeeding, physiological stress), mother-infant relationship (mother-infant bond, quality of maternal caregiving behavior). *Secondary infant outcomes*: behavior (fussing and crying, sleep quality), physical health (growth and health, physiological stress), general development (regulation capacities, social-emotional capacities, language, cognitive and motor capacities). *Secondary underlying mechanisms*: maternal oxytocin concentrations, infant intestinal microbiota.

**Discussion:**

As a simple and cost-effective intervention, SSC may benefit both the mother and her full-term infant in the short-and long-term. Additionally, if SSC is shown to be effective in low-risk mother-infant dyads, then thought could be given to developing programs in high-risk samples and using SSC in a preventive manner.

**Trial registration:**

NTR5697; Registered on March 13, 2016.

**Electronic supplementary material:**

The online version of this article (doi:10.1186/s12887-017-0906-9) contains supplementary material, which is available to authorized users.

## Background

Having a new baby is an extraordinary experience that most often brings much joy and happiness. At the same time, the first months after birth can also be challenging for parents. A large number of mothers experience postpartum depressive symptoms, which can affect both the mother and the infant. In preterm infants, daily skin-to-skin contact (SSC) between the mother and her infant has been shown to decrease maternal postpartum depressive symptoms. In full-term infants, only two studies investigated the effectiveness of SSC on maternal postpartum depressive symptoms and found similar results. Studies in preterm infants showed that SSC improves other mental and physical health outcomes in mothers as well as the infants, and promotes the quality of mother-infant relationship. Based on these previous findings, it can be hypothesized that SSC may have additional positive effects in mothers and their full-term infants as well. This randomized controlled trial (RCT) will be the first to investigate the effectiveness of a SSC intervention in decreasing maternal postpartum depressive symptoms and improving additional outcomes in mothers and their full-term infants, including maternal mental health, maternal and infant physical health, infant crying and sleeping behavior, the quality of the mother-infant relationship, and the long-term infant general development even up to 1 year of age. Additionally, two potential underlying mechanisms for the effectiveness of SSC on maternal and infant outcomes will be examined, namely maternal oxytocin concentrations and infant intestinal microbiota.

### Maternal postpartum depressive symptoms

Between 20 to 40% of mothers show subclinical levels of depressive symptoms within the postpartum period [1–3]. Compared to mothers without depressive symptoms, these mothers tend to be more irritable and show less maternal warmth and sensitivity to their newborn [4]. In turn, this can disturb the mother-child interaction, which in the long-term has been related to multiple negative child outcomes such as poorer emotional and cognitive development [4–6]. Moreover, mothers who have experienced postpartum depressive symptoms in the past, are significantly more likely to experience recurrent depressive symptoms even up to 4 years after birth [7]. Especially, these recurrent depressive symptoms seem to be related to negative child outcomes [6].

A wide range of prevention and intervention programs are available for mothers who experience postpartum depression, including pharmaceuticals and psychotherapy. The results with regard to the effectiveness are mixed [4, 8]. In addition, postpartum depression often remains undetected or remains untreated for a long period of time [9, 10]. Most mothers with subclinical levels of depressive symptoms will often not receive any treatment at all. Ideally, it would be best to prevent the mother from having depression and depressive symptoms. Hence, there is a great need for low-cost and easy-to-implement prevention or (complementary) intervention programs that are accessible for every mother, and that can be commenced immediately after birth.

### Skin-to-skin contact

Daily SSC between the mother and the infant is a promising, simple, and natural intervention that may be effective in decreasing postpartum depressive symptoms in mothers. During SSC, the naked infant, wearing only a diaper, is placed onto the bare chest of the mother [11]. The SSC method was designed as an alternative treatment to incubators for low birth weight and preterm infants.

In preterm infants, multiple studies showed that daily SSC results in lower levels of maternal depressive symptoms [12, 13]. To date, it is mainly unknown whether this positive effect extends to mothers of full-term infants. In a case study, a mother with numerous indicators of postpartum depressive symptoms was encouraged to provide SSC to her full-term infant. Daily SSC in the first days after birth reduced the levels of reported depressive symptoms of this mother and the symptoms remained absent even up to 7 months after birth [14]. Another study in full-term infants conducted a one-month SSC intervention trial starting immediately after birth [15]. Mothers were encouraged to provide 6 h of SSC with their infant on a daily basis during the first week after birth, and then 2 h per day until the infant was 1 month of age. This study showed that mothers in the intervention group (*n* = 30), compared to mothers in the control group (*n* = 60), showed statistically significant lower levels of postpartum depressive symptoms at 1 week and at 1 month after birth. These results are promising, however, the studies included relatively small sample sizes and did not perform a RCT. In the current RCT, as a primary outcome, we will investigate whether a 5-week SSC intervention period starting at birth reduces depressive symptoms up to 1 year postpartum in mothers of full-term infants.

### Additional effects of SSC in mothers and their full-term infants

In addition to the possible effectiveness of SSC on maternal postpartum depressive symptoms, SSC may also be related to other positive effects for the mother. In studies with preterm infants, research has shown that daily SSC is associated with lower levels of maternal reported anxiety and stress [16]. Also, SSC is reported to facilitate positive feelings in the mother and enhance her bonding to the infant, which in turn improves the quality of maternal caregiving behavior (e.g. more sensitive and less intrusive caregiving behavior) [16, 17]. Lastly, SSC in preterm infants improved the duration of breastfeeding [18].

In mothers of full-term infants, SSC during the first hours after birth decreases maternal anxiety, improves maternal caregiving behavior and is associated with longer breastfeeding duration [19, 20]. Only one study studied the effects of SSC on maternal outcomes beyond the first postnatal hours. Next to maternal postpartum depressive symptoms, this study found that a one-month intervention period of SSC was associated with a quicker maternal postpartum decrease in cortisol concentrations [15]. Cortisol can be described as a measure of physiological stress, since cortisol is the end product of the hypothalamic-pituitary-adrenal axis that is activated in response to stressful events [21].

Previous research in adults has shown that relaxation interventions can improve sleep quality, physical health, and recovery after surgery [22–24]. Moreover, multiple reviews show that touch, including physical intimacy and massage therapy, decreases physiological stress and pain and improves sleep and health [25, 26]. As SSC may constitute a daily hour of maternal relaxation that also includes touch, SSC may also improve maternal sleep quality, physical health, and physical recovery from the delivery.

The potential positive effects of SSC are not restricted to the mothers, as SSC may also be related to various beneficial outcomes in the full-term infant. In preterm infants, daily SSC has been related to better infant health and reduced stress, including increased weight gain, fewer infections, less crying, better sleep and attenuated cortisol stress responses [16, 27, 28]. Long-term effects of SSC are also seen, as SSC in preterm infants is related to better cognitive and motor development at 6 months of age and even to better cognitive control at age ten [13, 16].

In full-term infants, a systematic review showed that SSC immediately after birth for the first postnatal hours was related to less crying and fussing [19]. SSC also seems to have a protective effect during medical procedures. Full-term infants who were in SSC during a heel lance procedure cried less [29]. Also, 5-to-6 week old full-term infants’ cortisol concentrations decreased when resting in SSC, when compared to resting alone in a crib or playpen [30]. Another study compared sleep quality in 2-day old infants sleeping alone in a crib next to the mother or sleeping in SSC with their mother. Infants in SSC slept for a longer period of time, spent most of the time in quiet sleep and needed a shorter period to enter quiet sleep than when they were sleeping in a crib next to the mother [31]. In the current study, as secondary outcomes, we will investigate whether a 5-week daily SSC intervention period starting at birth improves maternal mental health, maternal and infant physical health, infant crying and sleeping behavior, the quality of the mother-infant relationship, and the long-term infant general development up to 1 year of age.

### Potential underlying mechanisms

The underlying working mechanisms that relate SSC early in life to improved maternal and infant outcomes are mainly unknown. One possible underlying mechanism is maternal oxytocin concentrations. The hormone oxytocin is released after the activation of multiple sensory nerves and in response to low intensity stimulation of the skin, including touch, as well as to suckling of the nipple [32, 33]. Oxytocin concentrations increase during social interaction, including parent-infant interactions [34]. The elevated concentrations of oxytocin are related to improved maternal mental health, by means of lower levels of maternal anxiety and stress, and improved bonding between mother and child [35]. To conclude, SSC may increase the maternal concentrations of oxytocin through the activation of multiple sensory nerves. In turn, these increased concentrations of oxytocin may explain the improved maternal mental health, the better quality of maternal caregiving behavior, and the longer duration and higher frequency of breastfeeding.

Another possible underlying mechanism of SSC is the infant intestinal microbiota. Infants are born with virtually sterile intestines. In vaginal deliveries, colonization of bacteria in the intestines starts during birth with bacteria originating mainly from the mother [36]. The intestinal ecosystem or microbiota consists mainly of bacteria and rapidly matures in the first months of life [37]. This early microbial colonization is important for the development of the immune system and the gastrointestinal tract [37, 38]. Less stable or diverse intestinal microbiota may delay the development of the immune system and is associated with diseases and excessive crying in the infant [39, 40].

Potentially, SSC facilitates the development of the infant intestinal microbiota, subsequently influencing infant outcomes, through direct and indirect pathways. First, daily periods of SSC could provide extra opportunities to exchange bacteria from the mother’s skin to the infant, hence enhancing microbiota development. Research has shown that infants born with a C-section receive fewer of their mother’s bacteria, but bacteria can still be passed on from the skin of the mother to the infant although in a lower frequency [41]. Second, as already mentioned above, SSC potentially reduces maternal depressive symptoms, anxiety, and reported and physiological stress levels in the mother. The improved maternal mental health may positively affect her quality of breast milk, which in turn is important for the healthy maturation of the infant intestinal microbiota during the first year of life [42]. Third, research has shown that there is a bidirectional communication between the gut and the brain, in which the stress hormone cortisol plays an important role [43]. In animal models, stress experienced by an organism can modify the balance of the gut microbiota, making the path clear for colonization by pathogenic bacteria, which in turn may affect immune and brain functioning [44]. SSC may be related to less stress in the infant, which in turn may facilitate the optimal colonization of the intestines of the infant. In sum, there are multiple ways through which an improved infant intestinal microbiota may mediate the relation between SSC and positive infant outcomes.

### Objectives

The primary goal of this RCT, with two parallel groups (intervention versus passive control group), is to examine if daily mother-infant SSC is effective in decreasing (sub)clinical levels of maternal depressive symptoms in a non-clinical sample with full-term infants in comparison to mothers who care for their infant as usual. The intervention starts immediately after delivery and has a duration of 5 weeks. The secondary aim is to investigate additional maternal and full-term infant outcomes, and two possible underlying mechanisms: maternal oxytocin concentrations and infant intestinal microbiota. We hypothesize that, compared to the control (care-as-usual) group, the SSC group will show:

*Improved maternal outcomes:*

1. Mental health:lower levels of depressive symptoms (primary outcome);lower levels of anxiety;lower levels of stress;lower levels of traumatic stress following child birth;better sleep quality.

2. Physical health:better physical recovery from the delivery;better health (fewer illnesses and health problems);more frequent and a longer duration of breastfeeding;lower levels of physiological stress.

3. Mother-infant relationship:better bonding to the infant;better quality of maternal caregiving behavior.

*Improved infant outcomes:*

1. Behavior:lower amounts of daily fussing and crying;better sleep quality.

2. Physical health:better growth and health (fewer illnesses and health problems);lower levels of physiological stress.

3. General development:better regulation capacities;better social-emotional capacities;better language, cognitive, and motor capacities.

*Potential underlying mechanisms:*
higher levels of maternal oxytocin concentrations. Maternal oxytocin concentrations will mediate the relationship between SSC and maternal outcomes.more optimal levels of intestinal microbiota (i.e. faster developing microbiota, more diverse and more stable microbiota, and fewer potentially pathogenic bacteria). Infant intestinal microbiota will mediate the relationship between SSC and infant outcomes.

## Methods

### Study design

This SSC intervention project in mothers and their full-term infants is a RCT with two parallel groups (intervention versus passive control group). The study has been designed in accordance with the SPIRIT 2013 statement (see Additional file 1 for complete checklist) [45]. Administrative information related to the trial can be obtained in Additional file 2. The project will start in April 2016. The expected total duration of the study from the start of recruitment to the last participant finishing the 1-year assessment is 20 months. The study will start with baseline measures in the last trimester of pregnancy. The intervention period will start immediately after birth and will have a duration of 5 weeks. Maternal and infant outcomes will be measured at 2 weeks, 5 weeks, 12 weeks and 1 year after birth.

### Ethics

The trial has been approved by the ethics committee of the Social Science faculty of the Radboud University in Nijmegen, The Netherlands (ECSW2015–2311-358). Modifications to the protocol, including changes of study objectives, study design, population, sample sizes, study procedures, or significant administrative aspects will require a formal amendment to the protocol. The potential amendment will be examined and approved by the ethics committee of the Social Science faculty of the Radboud University prior to implementation. Modifications to the protocol will also be included in the formal trial registration at the Dutch Trial Registration (NTR). This study does not involve any harmful procedures or adverse events. Since trial-related harm is negligible no provisions will be included, the study will not be audited, and no data-monitoring committee will be needed. Although we do not expect that the participants will experience trial-related harms, mothers will be asked weekly, for the first 5 weeks after birth, about any problems and mothers will be encouraged to report harms or adverse events spontaneously. Also, during the home visit in week 5 we will ask mothers to report any previously unreported harmful or adverse events that occurred during the study trial. Answers will be assessed by the investigators and will be reported in study reports. In addition, all participants that are enrolled in the study will be covered by the indemnity for negligent harm insurance (standard arrangements of the Behavioural Science Institute, Radboud University, Nijmegen, The Netherlands).

### Sample size calculation

The sample size was calculated with a power analysis, using the G Power 3 online tool [46]. The effect size of f = .24 for maternal depressive symptoms was based on the study of Bigelow and colleagues and was calculated by using the mean levels and the pooled standard deviation of maternal depressive symptoms for the SSC and the control group [15]. The power analysis indicated that a total group size of 84 mother-infant dyads was required to maintain a power of 80% to detect a minimum effect size of f = .24 for maternal depressive symptoms with a significance level of 0.05. Based on a prior longitudinal study in a similar population [47], we assume that 14% of the mothers will sign up to the study but will never participate. Based on the same longitudinal study [47], we calculated that the drop-out rate will be 4% and the loss in follow up rate will be 9%. Additionally, we estimate a non-compliance rate of 10%. In total, we need to include 31 additional pregnant women in order to retain power. To maintain equal groups we will recruit 116 participants (58 mothers and their infants in each arm).

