### Randomization

Primiparous mothers are expected to have more opportunities to provide SSC to their infants compared to multiparous mothers. A stratified random block randomization method will ensure a balance between the SSC and the control condition for the primiparae versus multiparae mothers. Also, this randomization method produces comparable groups by avoiding confounding from known and unknown factors [49]. The block sizes will be randomly chosen from the set of 4 and 6. Randomization will be with a 1:1 allocation. An independent researcher, who is not involved in the study, will prepare this schedule by a computerized randomisation program and will conceal the allocation sequence in stapled envelopes. The allocation sequence will be concealed from the researcher enrolling and assessing participants. The mothers will be included in the study after signing the informed consent, regarding the use of participant data and biological samples (see Additional file 3 for the Dutch versions of the informed consent form and information statement for participants), and filling out the medical checklist during the pregnancy home visit. Hereafter, the principal investigator will open the envelope and the mothers in the SSC group will be informed about their group allocation. Participants and the principle investigator will not be blinded for the group allocation.

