### Intervention and control condition

The study of Bigelow and colleagues requested their mothers to provide at least 6 h of SSC per day in the first week after birth and continue with at least 2 h of SSC per day until the infant was one moth of age [15]. However, many mothers did not meet the SSC criterion. In this study we reduce the amount of requested hours and extend the number of requested weeks of daily SSC to enlarge the number of mothers that meet the SSC criterion. In the Netherlands mothers are entitled to at least 10 weeks of paid maternity leave after delivery, which will facilitate adherence to our adapted SSC protocol. During the instruction phase of the pregnancy home visit, all mothers in the intervention group will be provided with detailed written and oral instructions on SSC. We will request and encourage mothers in the SSC condition to provide their infants with at least one uninterrupted hour of maternal SSC, on a daily basis and for 5 weeks, starting immediately after birth. Other caregivers are allowed to provide supplementary hours of SSC to the infant. The period of one uninterrupted hour is based on two arguments. First, the average duration of the sleep cycle of healthy full-term infants is 47 min [50]. The requested uninterrupted hour decreases the chance that infants need to be disturbed in the middle of a sleep cycle. Second, shorter SSC episodes could potentially decrease or eliminate the effectiveness of SSC, since undressing and dressing can be defined as a mild physical stressor for infants [51]. The requested uninterrupted hour requires to undress and dress the infant only once. During SSC, the naked infant, wearing only a diaper, will be placed in a stable and upright position between the breasts of the mother to facilitate and maximize SSC. The head of the infant is positioned in a slightly upright position to keep the airway open. After, the infant and mother will be covered by a blanket or cardigan (see also the practical guidelines of the World Health Organization [11]). Mothers in the SSC condition will explicitly be asked to feed their child before SSC. However, we will not discourage breastfeeding during SSC. During the oral and written instructions, we will explain safety precautions during SSC. We will emphasize the importance of being awake and alert during SSC, and of avoiding drinking hot beverages during SSC to protect the infant. During the second home visit (week 5 after birth), we will ask mothers whether they experienced problems with the safety precautions. Mothers in the control condition will not be requested and encouraged to provide SSC to their infant.

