
Mother in both groups will fill out the same daily contact logbook. In the daily logbook, all mothers will be asked to register for every 15 min with simple lines the following three categories: 1) holding, 2) SSC, and 3) no contact. In this logbook, mothers are also able to discriminate between holding and SSC by the mother or other caregivers, for example the father or grandparents.

Upon signing the informed consent, participants are informed that they may decide to discontinue the study at any moment and without giving a reason. Several measures are taken in order to minimize attrition and maintain adherence to the study. During the 5-week trial period, the principal investigator will have weekly contact with the participating mothers. Participants will be reminded of the upcoming data collection and they will be asked about any problems they are having with skin-to-skin contact, in filling out the logbooks, or with the collection of the stool samples. In addition, to improve participant retention the mothers will receive a small present after birth, and a present and a financial reimbursement of 20 euros at the home visit in week 5. Last, the mothers will receive the study-wide results after publication of the study reports.

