### Data-analysis

Data will be handled according to standard procedures. Demographic characteristics and study outcomes will be described for each treatment group using means and standard deviations for continuous outcomes. Proportions for categorical data will be provided. The pattern of missingness will be checked before the analyses. All measures will be controlled for outliers and checked for normality. Skewed continuous outcomes will be transformed. The level of significance (*p* -value) is set at *p* < .05 in all analyses.

We will conduct intention-to-treat analyses, in which participants are compared according to the group they were randomly assigned to regardless of participants’ compliance, including SSC protocol adherence, or withdrawal from the study, and analyses on imputed datasets based on the multiple imputation method [52]. Primary and secondary outcomes, that will be examined once, will be compared within multivariate analyses of covariance. Multilevel mixed models will be used for repeated measures. Microbiota composition will be examined with the Pearson’s moving window correlation. Microbiota diversity will be calculated with the Simpson’s reciprocal index of diversity (1/D). The Benjamini and Hochberg method will analyse differences between the SSC group and the control group. The analyses will be adjusted for potential confounding factors identified a priori (see Table 3). Structural equation models will be used to examine the mediation effect of the potential underlying mechanisms, maternal oxytocin concentrations and infant intestinal microbiota, on maternal and infant outcomes, respectively.

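### The 10% non-compliance allowance is counted as lost participants, but the intention-to-treat analysis keeps non-compliers, so it is the wrong correction for retaining 80% power

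*Protocol article*

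**What the plan says.** Sample size calculation: the protocol plans for "a minimum effect size of f = .24 for maternal depressive symptoms with a significance level of 0.05" and reports that "a total group size of 84 mother-infant dyads was required to maintain a power of 80" per cent. It then lists 14% who sign up but never take part, 4% drop-out and 9% loss to follow-up. It continues: "Additionally, we estimate a non-compliance rate of 10" per cent. From these it derives 31 additional women to preserve power and, after rounding to equal arms, a target of 116 (58 per arm). The effect size comes from the group means and pooled standard deviation of an earlier full-term SSC study.

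Data-analysis: under intention-to-treat, "participants are compared according to the group they were randomly assigned to regardless of" their compliance, explicitly including adherence to the SSC protocol.

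Intervention and control condition: of the study that supplied the effect size, the protocol says "However, many mothers did not meet the SSC criterion". It cites this as the reason for asking for fewer hours per day over more weeks.

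**The concern.** Attrition and non-compliance act on power in different ways. A mother lost to the study removes information, and recruiting a replacement restores it. A mother who stays but does not deliver the intervention is still analysed in the SSC arm, where she pulls that arm's mean towards the control mean. If a share c of the arm gains nothing, the mean difference shrinks by the factor (1 - c) and the required number rises by 1/(1 - c)^2. The Sample size calculation treats the 10% as the first kind of loss, while the Data-analysis section makes it the second.

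At stake is the claim that 116 retains 80% power for the primary outcome. If the claim is too high, a null result on depressive symptoms would be read as stronger evidence of no effect than it is.

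**Working it through.** **1. Reproduce the plan's figure.** Inputs, all from the Sample size calculation: base 84; rates 14%, 4%, 9% and 10%.

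- 84 x (0.14 + 0.04 + 0.09 + 0.10) = 84 x 0.37 = 31.08, i.e. 31. Then 84 + 31 = 115, made even = 116.
- Without the 10%: 84 x 0.27 = 22.7, which does not give 31.

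So the 10% enters as 84 x 0.10 = 8.4 lost women. The article nowhere reduces f = .24 for non-compliance.

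**2. Required number under intention-to-treat.** Assume that 10% of the SSC arm is non-compliant and gains nothing.

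- f = 0.9 x .24 = .216
- 84 / 0.9^2 = 84 / 0.81 = 103.7, i.e. about 104 analysable dyads. This is 23 to 24% more, not 10% more.

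**3. Power model.** The protocol states neither the number of occasions m nor the correlation r behind the 84. I assume a between-groups F test on repeated measures with 1:1 allocation, alpha .05 and non-centrality lambda = N x f^2 x m / (1 + (m - 1) x r), on 1 and N - 2 degrees of freedom. With m = 5 and r = .5, N = 84 gives lambda = 84 x .0576 x 1.667 = 8.06 and power 80.1%, which matches the plan. With m = 4 and r = .5, 84 gives 78.5% and 88 are needed. Five occasions would count the prenatal depression score; Table 1 lists four postnatal ones. Other pairs also fit 84, for example m = 3 with r = .4.

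**4. How many are analysed.**

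- All three attrition rates taken off 116: 116 x 0.86 x 0.96 x 0.91 = 87.
- Attrition as the plan sums it: 116 - 84 x 0.27 = 93.
- The 14% lost before the 116 are randomised: 116 x 0.96 x 0.91 = 101.

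**5. Power (r = .5), five occasions / four occasions.**

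| Effect | N = 87 | N = 93 | N = 101 |
|---|---|---|---|
| f = .216 (non-compliers gain nothing) | 73.0% / 71.2% | 75.8% / 74.1% | 79.3% / 77.6% |
| f = .228 (non-compliers keep half: .24 x 0.95) | 77.5% / 75.8% | 80.2% / 78.6% | 83.4% / 81.9% |
| f = .24 (no further dilution) | 81.5% / 79.9% | 84.0% / 82.6% | 86.9% / 85.6% |

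**6. Sensitivity to r.** At f = .216, N = 101 and four occasions, power is 82.6% with r = .4, 77.6% with r = .5 and 72.9% with r = .6.

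**The case against.** The mismatch between the two sections is hard to dispute, but several arguments limit its consequences.

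- **The effect size may already be diluted.** It comes from observed group means in a study where many mothers missed the SSC criterion. If those mothers are in the means, multiplying by 0.9 counts non-adherence twice. The protocol does not say whether they are, so this stands as an open question. A reader might infer that the stated 80% refers to a full-adherence contrast; the document does not show that. If dilution is already in f = .24, the separate 10% headcount has no basis either, so the sentence still needs correcting.
- **Non-compliers may gain something.** The request is for an unbroken hour every day for five weeks. A mother who misses some days fails it but has still given SSC. This stands, and is why the half-effect row is shown.
- **The 14% may not belong to the 116.** They sign up but never take part, sign-up precedes consent and allocation, and the 116 is described as 58 per arm. On that reading 101 are analysed and the shortfall is one to two points. The plan's own sum includes the 14%, so the text is ambiguous. Mixed models would also use early scores from mothers lost later, which favours the higher counts.
- **The protocol argues for better adherence than in the source study**, with a lighter request, maternity leave and weekly contact. The remark about that study therefore does not show that 10% is too low.

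A reader might also infer a further loss from control mothers giving SSC, since "Mother in both groups will fill out the same daily contact logbook". A shared logbook shows only that control SSC would be recorded, not how common it will be. The protocol gives no rate, so any power figure for it would be invented.

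**Conclusion.** The point holds as a wrong form of correction. The 31 extra women reproduce only if non-compliers are counted as lost, and the stated analysis does not lose them. If non-compliers gain nothing and f = .24 carries no dilution of its own, about 104 analysable dyads are needed for 80% power.

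The shortfall at 116 is uncertain and may be absent. At f = .216 with r = .5 and five (four) occasions, power is about 73% (71%) with 87 analysed and about 79% (78%) with 101. With five occasions it is about 80% or more if non-compliers keep half the effect and 93 to 101 are analysed, or if f = .24 already reflects imperfect adherence. The number of occasions, r, the analysed number and the benefit to non-compliers are all assumptions, and plausible changes in r alone move power by about five points either way. What the documents support is that the claim to retain power is not established by the calculation given, not that the trial is badly underpowered.

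**What to change.** Keep the target of 116 and keep intention-to-treat as primary. In the Sample size calculation:

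1. Stop describing the 10% as a headcount allowance that retains power. Do not simply delete it from the sum: that would cut the target to about 107 (84 x 1.27) and lower power further.
2. State whether f = .24 comes from means that include the source study's non-adherent mothers.
3. If it does not, restate power at the diluted intention-to-treat effect (f = .216 at 10%) for the number expected to be analysed, with a short range for other degrees of dilution. State the number of occasions, the correlation and whether the 14% are lost before or after the 116 are counted.

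The cost is a rewritten paragraph and a somewhat lower stated power; no recruitment or data collection changes. A secondary complier estimate from the contact logbooks is possible but optional, and the correction does not depend on it.
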